**Methods:**

This multi-site randomized controlled trial (RCT) aims to evaluate the clinical, patient-centred, and economic effectiveness of a stepped-care intervention in a sample of 212 patients with panic-related anxiety presenting to the ED of Singapore’s largest public healthcare group. Participants will be randomly assigned to either: 1) an enhanced care arm consisting of a stepped-care intervention for panic-related anxiety; or 2) a control arm consisting of screening for panic attacks and panic disorder. Screening will be followed by baseline assessments and blocked randomization in a 1:1 ratio. Masked follow-up assessments will be conducted at 1, 3, 6, and 12 months. Clinical outcomes will be panic symptom severity and rates of panic disorder. Patient-centred outcomes will be health-related quality of life, daily functioning, psychiatric comorbidity, and health services utilization. Economic effectiveness outcomes will be the incremental cost-effectiveness ratio of the stepped-care intervention relative to screening alone.

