### Specific aims

*Aim 1 (Primary):* To evaluate the clinical effectiveness of a stepped-care intervention for ED patients with panic-related anxiety compared to screening alone.

*Outcomes under Aim 1:* The primary outcome under Aim 1 will be clinician-rated severity of panic symptoms, measured using the Panic Disorder Severity Scale (PDSS) [30] and the Clinical Global Impression Scale (CGI) [31]. Panic disorder will be diagnosed using the Structured Clinical Interview for DSM-5 (SCID) [32].

*Aim 2:* To evaluate the patient-centred effectiveness of a stepped-care intervention for ED patients with panic-related anxiety compared to screening alone.

*Outcomes under Aim 2:* We will examine health-related quality of life using the 12-item Short Form Health Survey (SF-12) [33], and the EuroQoL–5 Dimension (EQ-5D) [34]. We will assess psychiatric comorbidity using the Psychiatric Diagnostic Screening Questionnaire (PDSQ) [35], and healthcare utilization for panic-related symptoms (ED visits and hospital admissions) based on electronic medical record data in the 12 months following the intervention.

*Aim 3:* To evaluate the incremental cost-effectiveness of a stepped-care intervention for ED patients with panic-related anxiety compared to screening alone, from the health system perspective.

*Outcomes under Aim 3:* We will calculate the incremental cost-effectiveness ratio (ICER) of stepped-care intervention relative to screening alone, at 12 months from baseline. Direct healthcare costs will be calculated from electronic billing records and the effectiveness of the intervention will be assessed based on the conversion of SF-12 form to a quality of life weight using the Short Form Health Survey 6D (SF-6D) algorithm [36].

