*Inclusion Criteria:* 1. Diagnosis of panic attack or panic disorder confirmed by the SCID interview 2. Willing to enter randomized trial	*Exclusion Criteria:* 1. Does not meet criteria for panic attack or panic disorder based on the SCID interview 2. Received CBT for panic symptoms in the last 12 months 3. Unwilling to enter randomized trial

In order to maximize generalizability to the broad group of patients with panic symptoms who present to the ED, we will not exclude patients who have received other types of psychotherapy for panic symptoms or those who are being treated with antidepressant medications. However, we will assess for these treatments at each time point and we will control for ancillary treatments in subsequent analyses. Patients who have received CBT for panic symptoms in the prior 12 months will be excluded.

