### Data analysis

We will use the following statistical methods to evaluate the specific aims.

*Aim 1: To evaluate the clinical effectiveness of stepped-care* versus *screening alone:* All analyses will be based on the intention-to-treat (ITT) principle. We will employ a mixed model approach to analyse the primary outcome variable, with repeated measurements taken at the 1-, 3-, 6- and 12-month follow-up visits. These models allow for different number of observations per subject, use all available data on each subject, and are unaffected by randomly missing data. We will examine the fixed categorical effects of treatment pathway (STEP, SCREEN), visit time (1, 3, 6, and 12 months), and treatment pathway-by-visit time interaction. The restricted maximum likelihood approach will be utilized for estimation. Significance tests will be based on least squares means using a two-sided alpha = 0.05. Primary treatment comparisons will be contrasts in least squares means between treatment groups at the endpoint visit. The CGI scores and SCID diagnoses will be analysed in a similar fashion. As a follow-up to the ITT analyses, we will also conduct a completer analysis. Participants in the STEP arm who are stepped up to CBT and complete four out of five of the CBT sessions will be deemed completers. Those in the STEP arm who complete the psychoeducation session and are not stepped-up to CBT will also be considered completers for the purpose of analysis.

*Aim 2: To evaluate the patient-centred effectiveness of stepped-care* versus *screening alone:* We will use the same mixed model approach as outlined under Aim 1 to analyse data from the patient-reported outcomes (SF-12, EQ-5D, and PDSQ).

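### The model listed for SCID diagnosis leaves out baseline diagnosis, which is both the stratification factor and the baseline value of this outcome; its wording also suits a continuous score better than a yes/no diagnosis

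*Protocol article*

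**What the plan says.** The abstract names two clinical outcomes: "Clinical outcomes will be panic symptom severity and rates of panic disorder". Under Specific aims, Aim 1, the second is tied to the SCID: "Panic disorder will be diagnosed using the Structured Clinical Interview for DSM-5 (SCID").

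The Data analysis section, Aim 1, sets out one method for the primary outcome: "We will employ a mixed model approach to analyse the primary outcome variable, with repeated measurements taken at the 1-, 3-, 6- and 12-month follow-up". The listed terms are the "fixed categorical effects of treatment pathway (STEP, SCREEN), visit time (1, 3, 6, and 12 months), and treatment pathway-by-visit time interaction". On estimation: "The restricted maximum likelihood approach will be utilized for estimation". On the comparison: "Primary treatment comparisons will be contrasts in least squares means between treatment groups at the endpoint visit". The method is then extended: "The CGI scores and SCID diagnoses will be analysed in a similar fashion".

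Patients enter with either of two diagnoses. The stage 2 inclusion criterion in Table 1 reads "Diagnosis of panic attack or panic disorder confirmed by the SCID interview". The Randomization section makes this diagnosis the stratification factor, and Table 2 shows the SCID panic module at baseline and at every follow-up. The only further adjustment announced is for ancillary treatments (Participants & procedures). Neither baseline diagnosis nor stratum is in the listed model.

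**The concern.** Stratified randomisation balances the arms on baseline diagnosis, so the treatment difference varies from trial to trial only through the variation within strata. A model without the stratum estimates its standard error from the total variation, which includes the difference between strata. If diagnosis at entry predicts diagnosis at follow-up, the reported standard error is too large, the test rejects too rarely under the null, and power is lost. For SCID diagnosis the link is direct, because the omitted factor is the same variable measured at baseline.

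The second, smaller matter is the scale. A diagnosis is categorical, while restricted maximum likelihood and least squares means are the usual terms for a continuous score. No link function, odds ratio, risk difference or other categorical method is named. If the wording were applied literally to a yes/no outcome, an arm's interval could leave the range 0 to 1 when rates are low. The section's claim that its models cope with randomly missing data would also rest on a likelihood that does not describe the data, in a trial that plans for 25% attrition.

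**Working it through.** **The plan's own figure.** The Sample size section concerns the PDSS: d = 0.516, two-sided 0.05, 90% power.

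- n per arm = 2(1.960 + 1.282)² / 0.516² ≈ 79 (normal approximation); the t-test version gives 79.9, so 80.
- Power at 80 per arm: 0.904 (normal), 0.900 (t-test).
- Attrition: 80 / 0.75 = 106.7, so 107 per arm or 214 in total, against 212 stated (212 × 0.75 = 159).

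The stated figure reproduces within rounding. It does not depend on SCID diagnosis.

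**Type I error without the stratum.** From the plan: 80 evaluable per arm, 1:1 allocation, stratification on diagnosis, alpha 0.05. Assumed: panic disorder at the endpoint visit in 60% of those who entered with panic disorder and in 10% of those who entered with panic attack only, the same in both arms. Let f be the share entering with panic disorder.

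- Overall rate p = 0.6f + 0.1(1 − f); total variance = p(1 − p).
- Within-stratum variance = 0.24f + 0.09(1 − f).
- The standard error is too large by the factor k = √(total / within). The nominal 1.96 cut-off then acts as 1.96k, and the true two-sided type I error is 2[1 − Φ(1.96k)].

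| f | total variance | within variance | k | 1.96k | type I error |
|---|---|---|---|---|---|
| 0.3 | 0.25 × 0.75 = 0.1875 | 0.072 + 0.063 = 0.135 | 1.18 | 2.31 | 2.1% |
| 0.5 | 0.35 × 0.65 = 0.2275 | 0.120 + 0.045 = 0.165 | 1.17 | 2.30 | 2.1% |
| 0.7 | 0.45 × 0.55 = 0.2475 | 0.168 + 0.027 = 0.195 | 1.13 | 2.21 | 2.7% |

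**Simulation.** One visit, 80 per arm, exact balance on diagnosis, no missing data, 2,000 runs per scenario. For power, the assumed rates are 70% (SCREEN) against 45% (STEP) in the panic disorder stratum, and 15% against 7% in the panic attack stratum.

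| | f = 0.3 | f = 0.5 | f = 0.7 |
|---|---|---|---|
| Type I error, no stratum, linear | 1.7% | 2.9% | 2.6% |
| Type I error, no stratum, logistic | 1.7% | 2.9% | 2.6% |
| Type I error, stratum, linear | 5.6% | 5.2% | 4.8% |
| Type I error, stratum, logistic | 5.1% | 5.0% | 4.8% |
| Power, no stratum, linear | 50.5% | 62.8% | 71.6% |
| Power, no stratum, logistic | 50.1% | 62.8% | 71.6% |
| Power, stratum, linear | 62.8% | 72.0% | 79.0% |
| Power, stratum, logistic | 62.1% | 71.8% | 79.0% |

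Power lost by leaving out the stratum (linear): 62.8 − 50.5 = 12.3, 72.0 − 62.8 = 9.2 and 79.0 − 71.6 = 7.4 points. Linear and logistic differ by at most 0.7 points in any pair, so at these rates the stratum drives the result and the model family does not.

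**Low rates.** Assumed 12% against 3% (panic disorder stratum) and 2% against 1% (panic attack stratum), f = 0.5. The linear model's interval for the STEP mean fell below zero in 95% of runs. The logistic model had trouble of its own here: it failed to fit in 175 of 2,000 runs, and its Wald test with the stratum rejected in 9.2% of runs against 34.4% for the linear model (failed fits counted as non-rejections).

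**The case against.** The strongest defence is that this is a condensed article, and that covariates and link functions for a non-primary outcome belong in an analysis plan that is not shown. For the link function much of this stands. A reader might infer that the protocol prescribes a linear Gaussian model for SCID diagnosis, but it never uses the word linear. A similar analysis could be a logistic mixed model with the same terms; such models can be fitted by restricted pseudo-likelihood and can report least squares means on the link scale. For the stratum the defence is weaker, because the article does list its fixed effects and names one further adjustment, and baseline diagnosis is in neither place.

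A reader might also conclude that the linear model is invalid here. The check does not support that: with the stratum included, linear and logistic models had nearly the same type I error and power at moderate rates, and a linear arm-by-visit analysis estimates a risk difference. Impossible limits are not a general result either. They concern a single arm's mean under assumed low rates; at an overall rate of 30% the interval is 0.30 ± 1.96√(0.21/80), about 20% to 40%. The treatment contrast may properly be negative.

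Two further points stand. The listed model also omits baseline PDSS, so the gap is not peculiar to SCID. And because randomisation is stratified, the omission costs precision without biasing the comparison.

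**Conclusion.** The point holds for the stratum and, more modestly, for the model form. As listed, the SCID model leaves out the factor on which randomisation is stratified. Under the assumed rates this gives a true type I error of about 2 to 3% instead of 5% and costs roughly 7 to 12 power points. The direction needs only that diagnosis at entry predicts later diagnosis. The size depends on assumed rates and on the assumed share of patients entering with panic disorder, since the protocol gives neither. It also comes from a single-visit calculation with exact balance and no missing data.

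The logistic form is the better choice for a yes/no outcome, but its gain lies in interval limits at low rates and in supporting the missing-data claim; the latter was not simulated. The documents do not show that baseline diagnosis is the strongest predictor, that the treatment test would be invalid, or that the primary analysis or sample size is affected. The change is worth making because SCID diagnosis supplies one of the two clinical outcomes in the abstract.

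**What to change.** - Define the SCID endpoint as panic disorder, yes or no, at each visit.
- Add the baseline-diagnosis stratum (panic attack or panic disorder) as a fixed effect beside arm, visit and arm-by-visit.
- Name a logistic mixed model or logistic GEE, and report the marginal risk difference and odds ratio at the endpoint visit, averaging predictions over the strata. The mixed model fits the missing-data claim better, since ordinary GEE needs a stricter missingness assumption.
- State beforehand what will be done if the logistic model does not converge, and do not rely on its Wald test alone when events are few.

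Results by stratum (remission in one, onset in the other) are optional.

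The cost is wording only: the SCID is already scheduled at baseline and every follow-up, and design and sample size stay as they are. The downside is slow or failed convergence with few events, as the low-rate scenario shows. The wording should be settled before unblinded data are analysed, so that scale and adjustment are not chosen after the results are seen.

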### Interventions

Participants in both the SCREEN and STEP arms will follow the typical care pathway in the ED, which includes medical evaluation of their presenting complaint, any investigations ordered by the ED physician, reassurance that their symptoms are not indicative of acute coronary syndrome or other life-threatening illnesses, and outpatient follow-up as recommended at discharge. Participants in the SCREEN arm will be given the results of the screening interview, but no other protocol interventions. Participants in the STEP arm will be given a 1-hour psychoeducation session consisting of information regarding the nature and causes of panic attacks and behavioural strategies to manage future attacks. They will also be provided with written materials for future reference. Patients in the STEP arm who do not improve with psychoeducation will receive CBT based on a brief manualized protocol consisting of five weekly 1-hour individual sessions; the sessions will focus on cognitive restructuring and exposure to panic symptoms [42]. The psychoeducation and CBT sessions will be delivered by a trained clinical psychologist in either English or Mandarin, depending on the patient’s preference.

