### Criteria for ‘stepping up’ in the stepped-care intervention arm

The decision to step-up interventions for patients in the STEP arm will be guided by remission status as assessed by the PDSS and CGI. Acute remission status is defined by a CGI score of 1 or 2 (no disorder or borderline disorder) and no panic attacks for a one-week period. Full remission is defined by maintenance of this status for two consecutive months [49]. Participants who show acute remission of panic symptoms one month after completing the psychoeducation session will enter the follow-up phase. Those who do not show acute remission of panic symptoms at one-month post-psychoeducation or return to the ED with panic symptoms within three months will be stepped up to receive the 5-session CBT protocol.

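### Completer status in STEP depends on early outcome and has no counterpart in SCREEN, so a completer comparison is not protected by randomisation and probably favours STEP

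*Protocol article*

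**What the plan says.** The Data analysis section (Aim 1) makes ITT the basis of the analyses and then adds: "As a follow-up to the ITT analyses, we will also conduct a completer analysis". Two rules say who is a completer, and both concern STEP:

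- Stepped-up patients: "Participants in the STEP arm who are stepped up to CBT and complete four out of five of the CBT sessions will be deemed completers".
- Patients not stepped up: "Those in the STEP arm who complete the psychoeducation session and are not stepped-up to CBT will also be considered completers".

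The section on criteria for stepping up says which rule a patient falls under. The decision is "guided by remission status as assessed by the PDSS and CGI", where acute remission means a CGI of 1 or 2 and a week free of panic attacks. "Participants who show acute remission of panic symptoms one month after completing the psychoeducation session will enter the follow-up phase". CBT is for "Those who do not show acute remission of panic symptoms at one-month post-psychoeducation or return to the ED with panic symptoms within three months".

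For the control arm, the Interventions section says: "Participants in the SCREEN arm will be given the results of the screening interview, but no other protocol interventions". No completer rule is given for SCREEN.

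**The concern.** Both triggers for stepping up are measured after randomisation, and both belong to the trial's own outcomes. PDSS and CGI are the Aim 1 severity measures, and ED visits for panic-related symptoms are an Aim 2 outcome. A STEP patient who is well at one month and stays away from the ED enters the completer set with one session. A STEP patient who is not well must pass a second filter of four CBT sessions, and those who fail it are removed. The STEP completer set is therefore enriched for good early outcomes, while in SCREEN patients who are equally unwell at one month all stay in.

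This goes further than the usual weakness of a completer analysis, where adherence may merely correlate with prognosis. Here the adherence requirement itself is set by an early outcome. At stake is the reading of a secondary result: it could suggest a benefit among those who completed when the ITT contrast shows none, or enlarge a true effect.

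**Working it through.** **The plan's own figure.** The article gives no figure for the completer analysis, so the only one to reproduce is the sample size: d = 0.516, 90% power, two-sided 0.05. The normal approximation gives 2 × (1.960 + 1.282)² / 0.516² = 78.9, so 79 per arm. The noncentral t gives 80, as stated. With 25% attrition, 160 / 0.75 = 213.3, or 214 when rounded up to equal arms, against 212 stated (212 × 0.75 = 159). This is a rounding difference, and the point below does not touch it. The 80 evaluable patients per arm are used below.

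**Model with no true effect.** Let X be standardised severity at one month and Y standardised severity at a later visit, with correlation ρ and the same distribution in both arms. In STEP the lowest fraction r of X are remitters. All of them are kept, taking them to have attended psychoeducation and not to have returned to the ED. Non-remitters are kept with probability c, the chance of finishing CBT, unrelated to their prognosis. SCREEN is kept whole.

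With z the r-quantile of the standard normal and φ its density:

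- mean X of remitters: −φ(z)/r
- mean X of non-remitters: φ(z)/(1 − r)
- fraction of STEP kept: k = r + c(1 − r)
- share of remitters among those kept: w = r/k
- bias in Y: ρ × [w × (−φ(z)/r) + (1 − w) × φ(z)/(1 − r)] = −ρ φ(z)(1 − c)/k

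The last form is negative (favours STEP) for any c < 1 and ρ > 0, and zero at c = 1.

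**Inputs.** r, c and ρ are all assumptions; the article gives none of them.

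**Worked case**, r = 0.4, c = 0.6, ρ = 0.6: φ(z) = 0.3863 and k = 0.4 + 0.6 × 0.6 = 0.76. Remitters rise from 40% to 0.4/0.76 = 53% of the STEP set. Bias = −0.6 × 0.3863 × 0.4 / 0.76 = −0.122 SD. With 80 SCREEN and 80 × 0.76 = 60.8 STEP patients, SE = √(1/80 + 1/60.8) = 0.170. The test statistic shifts by −0.122/0.170 = −0.72, and the two-sided 5% test rejects about 11% of the time.

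| r | c | ρ | STEP kept of 80 | Bias (SD) | Rejection under no effect |
|---|---|---|---|---|---|
| 0.4 | 1.0 | any | 80.0 | 0 | 5.0% |
| 0.2 | 0.9 | 0.3 | 73.6 | −0.009 | 5.0% |
| 0.4 | 0.75 | 0.5 | 68.0 | −0.057 | 6.4% |
| 0.4 | 0.6 | 0.5 | 60.8 | −0.102 | 9.2% |
| 0.4 | 0.6 | 0.6 | 60.8 | −0.122 | 11.1% |
| 0.4 | 0.5 | 0.7 | 56.0 | −0.193 | 19.8% |
| 0.4 | 0.4 | 0.6 | 51.2 | −0.217 | 22.9% |

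**Ranges.** With r = 0.2–0.5, c = 0.5–0.9 and ρ = 0.3–0.7, the bias is −0.01 to −0.19 SD. With r = 0.3–0.5, c = 0.4–0.8 and ρ = 0.4–0.6, it is −0.03 to −0.22 SD, and between 0.5 × 0.2 = 10% and 0.7 × 0.6 = 42% of STEP is discarded. Pairing the lowest completion with the highest correlation (r = 0.4, c = 0.4, ρ = 0.7) gives −0.7 × 0.3863 × 0.6 / 0.64 = −0.25 SD.

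**Relaxing the dropout assumption.** A simulation let CBT completion among non-remitters depend on later severity, with log-odds of 0.5 to 1 per SD, for r = 0.3–0.4, c = 0.6–0.75 and ρ = 0.3–0.7. If sicker patients leave CBT more often, the bias is −0.09 to −0.29 SD. If improving patients leave more often, it is −0.08 to +0.13 SD, so it can change sign.

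**The case against.** Several things can fairly be said for the plan, and most of them limit the point without removing it.

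- **Comparator.** The article does not say which SCREEN patients the completers are compared with, or that a test will be made. A condensed article may leave that to the analysis plan. This stands as a caveat: the whole SCREEN arm is the natural reading, not a stated fact. The STEP rules themselves are stated, and they create the problem for any comparison with SCREEN.
- **Not every early remitter is kept.** A reader might infer that all one-month remitters in STEP count as completers. The text does not support this. The psychoeducation session must have been completed, and a remitter who returns to the ED with panic symptoms within three months is stepped up and must then meet the CBT rule.
- **Direction.** A reader might also infer that the analysis must favour STEP whatever happens. That needs CBT dropout not to be driven by improvement; the simulation shows that the bias can vanish or reverse. It also shrinks if a non-remitter who declines CBT is counted as not stepped up, which the article leaves open.
- **Size.** No input comes from the document. The larger values need low CBT completion, and with near-complete attendance the bias is negligible. These are biases at later visits, so they should not be set directly against the 0.516, which was planned for one month.
- **Status.** ITT comes first, and nothing in the article lets the completer result replace it. This stands in full: the primary conclusion is not at risk.

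**Conclusion.** The concern holds in a limited form. As written, completer status is defined in STEP only and is conditional on early outcome, so a completer contrast with SCREEN is not a randomised comparison. That follows from the text and needs no assumption about rates.

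The direction is probable, not certain. With no true effect, and CBT dropout unrelated to prognosis among non-remitters, the contrast favours STEP by about 0.01 to 0.22 SD over the two sets of assumed ranges, with 0.25 SD at the most extreme combination. It is worth correcting because the definition is already fixed in the protocol and correction costs little. It gives no reason to doubt the ITT analysis.

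**What to change.** In the Data analysis section (Aim 1), keep the completer definitions as a description of attendance. State that STEP attendance and completer outcomes will be summarised descriptively, with no test or estimate against SCREEN. Say also how a patient who declines CBT is classed. No new data and no change to the step-up pathway are needed. The cost is a few sentences and the loss of a naive completer p-value.

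If the investigators want an effect of receiving the programme, use an estimate that keeps all randomised patients in both arms, such as a complier-average causal effect with randomisation as the instrument. Three conditions should be written down:

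- Receipt is defined without reference to remission, for example attending the psychoeducation session. If receipt meant meeting the present completer rule, a non-completer could have had psychoeducation and up to three CBT sessions, and any benefit from these would break the exclusion restriction.
- The exclusion restriction is stated: assignment to STEP has no effect on patients who do not attend that session, including through any later CBT.
- Only baseline covariates are used. The ancillary treatments recorded at each visit, which the Participants & procedures section plans to control for, should not enter this model.

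The cost of this option is a wider interval and one extra, untestable assumption.

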### Outcome measures

Outcome measures were selected to 1) provide adequate coverage of the core symptoms of panic attacks, panic disorder, and comorbid psychiatric conditions (e.g., depression, generalized anxiety disorder, substance use disorders), 2) assess disability and quality of life as well as symptom severity, and 3) have acceptable psychometric properties in English and Chinese. Whenever possible, we chose outcome measures that have been widely used in other clinical trials on panic disorder to facilitate comparison with other studies (i.e., in subsequent meta-analyses). In addition to clinician-rated and patient-reported outcome measures, we will collect service-use data from patient medical and billing records, and will ask patients to report on their use of ancillary treatments (e.g., other types of counselling, traditional Chinese medicine, stress management programs) and psychotropic medications at each assessment visit.

Clinician-rated outcomes: We will use the following clinician-rated assessment instruments to assess the outcomes under Aim 1.

*Clinical Decision Rule (CDR)*: The study team has developed a brief 7-item screening tool that can quickly distinguish between ED patients with or without panic-related anxiety [8]. The CDR consists of the following symptoms: 1) palpitations, pounding heart, or accelerated heart rate, 2) derealization, 3) paresthesia, 4) sensations of shortness of breath or smothering, 5) chills or hot flushes, 6) feeling dizzy, unsteady, lightheaded, or faint, and 7) fear of losing control or going crazy. The CDR is scored by assigning 1 point for each positive symptom. It has demonstrated excellent overall separation between patients with or without panic-related anxiety (area under the receiver operating characteristic curve = 0.90). At a cut- off score of 3 or greater, the CDR has a good balance between sensitivity (81.7%) and specificity (87.9%) [8].

*Panic Disorder Module of the Structured Clinical Interview for DSM-5 (SCID)*: The SCID is the gold standard tool for the reliable diagnosis of Axis I psychiatric disorders in clinical populations [32]. The study team has extensive experience using the panic disorder module of the SCID in previous ED studies [8, 43]. We found that inter-rater reliability was excellent for panic attacks (κ = 1.00) and panic disorder (κ = 0.82), indicating that the interviewers were able to assess panic symptoms with a high degree of accuracy.

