### Participant timeline

Participants in both arms will be involved in the trial for a period of 12 months. Following recruitment at baseline at the ED, masked follow-up assessments will be conducted by an independent interviewer at 1, 3, 6, and 12 months. The timeline of study assessments is shown in Table 2. Participants in the STEP arm will receive psychoeducation within 1 week of discharge from the ED and those who are stepped-up will receive 5 weekly sessions of CBT between the 1-month and 3-month follow-up.

**Table 2 Tab2:** Timeline of study assessments

Construct	Outcome Measure	Time point					
		Screening	Baseline	1 month	3 months	6 months	12 months
Panic Screening	CDR^a^	x					
Panic Attack/Disorder Diagnosis	SCID Panic Module^a^		x	x	x	x	x
Panic Symptom Severity	PDSS^a^		x	x	x	x	x
	CGI^a^		x	x	x	x	x
Psychiatric Comorbidity	PDSQ^b^		x	x	x	x	x
Health-Related Quality of Life	SF-12^b^		x	x	x	x	x
Healthcare Utilization	Electronic medical record						x
Direct Healthcare Costs	Electronic billing data						x
Cost Effectiveness	SF-6D/EQ-5D^b^		x	x	x	x	x

^a^Clinician-rated outcomes. ^b^Patient-reported outcomes

*CDR* Clinical Decision Rule; *SCID5 RV* Structured Clinical Interview for DSM-5; *PDSS* Panic Disorder Severity Scale; *CGI* Clinical Global Impressions Severity Scale; *PDSQ* Psychiatric Diagnostic Screening Questionnaire; *SF-12* Short Form Health Survey; *EQ-5D* EuroQoL- 5 Dimension

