*Aim 3: To assess the cost-effectiveness of stepped-care* versus *screening alone from the health system perspective:* We will estimate the ICER for the STEP arm participants relative to the SCREEN arm participants at 12 months from baseline. The ICER is calculated as the difference between the costs of the two strategies divided by the difference in their effectiveness. Costs from the health system perspective will be the difference in average costs between those in the STEP and SCREEN arms, based on hospital billing data. The difference in effectiveness will be based on the quality of life weights generated by applying the SF-6D algorithm to scores from the SF-12 survey. The STEP intervention will be considered dominant over SCREEN if it incurs less costs and generates higher quality-adjusted life years (QALYs). STEP will be considered cost effective relative to SCREEN if the ICER is below the cost-effectiveness threshold. We will adopt the National Institute for Health and Care Excellence’s cost-effectiveness threshold of £20,000–30,000 per QALY gained, which roughly translates into $63,313 SGD per QALY gained [51].

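### Billing records are the only stated cost source for the ICER, so the plan does not ensure that the cost of delivering the STEP sessions is counted

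*Protocol article*

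**What the plan says.** Three places in the protocol article name a source for costs, and all three name billing. Specific aims, under the Aim 3 outcomes: "Direct healthcare costs will be calculated from electronic billing records". Table 2 (Participant timeline), in the row for direct healthcare costs: "Electronic billing data", at 12 months. Data analysis, Aim 3: health-system costs are "the difference in average costs between those in the STEP and SCREEN arms, based on hospital billing data". Outcome measures adds that "we will collect service-use data from patient medical and billing records", which concerns use of services and describes no costing of the intervention.

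The quantity to be estimated is broader. Aim 3 evaluates stepped care "compared to screening alone, from the health system perspective", and Data analysis states: "The ICER is calculated as the difference between the costs of the two strategies divided by the difference in their effectiveness".

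The resource that separates the arms is in Interventions: "Participants in the STEP arm will be given a 1-hour psychoeducation session", followed by five weekly one-hour individual CBT sessions for those who do not improve. "The psychoeducation and CBT sessions will be delivered by a trained clinical psychologist". SCREEN participants receive their screening result and no further protocol intervention.

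**The concern.** The definition of the ICER and the source of its numerator may not match. A health-system comparison of two strategies has to include what it costs to run each. STEP consists of psychologist time, and the health system bears that cost whether or not a bill is raised. Billing records see it only if the sessions are charged through the hospital, and nothing in the article says that they are.

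Some of the text suggests that they may not be. Interventions treats the sessions as protocol interventions, and Data monitoring lists CBT among the study procedures, next to screening interviews and questionnaires. Under Participant timeline, psychoeducation comes within a week after ED discharge and CBT between months 1 and 3, so neither belongs to the index ED visit.

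The savings hoped for in the Discussion (fewer ED visits, investigations and admissions) would appear in billing data. If delivery did not, STEP would be credited with its savings and not charged for what produced them. The article calls STEP dominant when it costs less and yields more QALYs, so a small billed saving could be enough for that verdict.

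**Working it through.** The article gives no unit cost, step-up share, expected QALY gain or expected ICER. There is thus no figure of its own to reproduce, and no single corrected ICER can be computed. What can be worked out is how much would be missing if the sessions are unbilled.

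**Inputs from the article**
- One hour of psychoeducation per STEP participant, and five hours of CBT for each one stepped up (Interventions).
- No psychologist sessions in SCREEN (Interventions).
- Threshold: SGD 63,313 per QALY (Data analysis, Aim 3).

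**Assumed inputs (not in the article)**
- Share stepped up: p = 0.3 to 0.7.
- Psychologist cost: c = SGD 100 to 200 per hour.
- QALY gain of STEP over SCREEN: 0.02 or 0.04.
- All scheduled sessions attended.

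**Step 1. Hours per STEP participant** = 1 + 5p.
- p = 0.3: 1 + 1.5 = 2.5 h.
- p = 0.7: 1 + 3.5 = 4.5 h.
- Limits: 1 h if nobody is stepped up, 6 h if everybody is.

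**Step 2. Omitted cost** = c × (1 + 5p).
- Low: 100 × 2.5 = SGD 250.
- High: 200 × 4.5 = SGD 900.

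**Step 3. Understatement of the ICER** = omitted cost / QALY gain.

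| Assumed QALY gain | Low | High | Share of 63,313 |
|---|---|---|---|
| 0.02 | 250/0.02 = 12,500 | 900/0.02 = 45,000 | 20% to 71% |
| 0.04 | 250/0.04 = 6,250 | 900/0.04 = 22,500 | 10% to 36% |

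**Step 4. QALY gain needed just to pay for delivery at the threshold** = omitted cost / 63,313.
- 250/63,313 = 0.004, and 900/63,313 = 0.014.
- With wider assumptions (c = SGD 50 to 300, p = 0 to 1) the omitted cost is SGD 50 to 1,800, and the gain needed is 0.0008 to 0.028.

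**Step 5. Dominance.** Let S be the mean billed saving per STEP participant and D the unbilled delivery cost. On billing data STEP is cheaper whenever S > 0. On full cost it is cheaper only when S > D. For any S between 0 and D, with a QALY gain, STEP would be declared dominant although it costs more than SCREEN. Under the assumptions in Step 2, that band is SGD 250 wide at the low end and SGD 900 at the high end.

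**Direction.** Only STEP has these sessions, so leaving them out can only lower its relative cost.

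**The case against.** A reader might infer that the ICER leaves out the cost of the programme and is therefore biased toward STEP. The article does not support that. It nowhere says that the sessions are free, grant-funded or unbilled. They are given by a clinical psychologist in a trial run at hospitals of one public healthcare group, and if they are charged through those hospitals, billing data would capture some or all of the cost. Delivery cost is not declared out of scope either, since the ICER is defined on the two strategies. This part of the objection stands, and the bias must be stated conditionally.

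It can also be said that a journal article condenses a longer protocol, and that unit costs and rules against double counting commonly sit there or in an analysis plan. That is fair for the details. It does not dispose of the point, because the article is not silent on costs: it states the rule for the numerator and ties it to billing data. An analysis that follows this rule as written has no route for adding unbilled sessions.

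The size is illustrative. Step-up share, hourly cost and QALY gain are all assumed, and the share of the threshold halves when the assumed gain doubles. Without the expected savings or a baseline ICER, nobody can show that the verdict would in fact change. Finally, Aim 3 is not the primary aim, and Aims 1 and 2 are untouched.

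**Conclusion.** The concern holds in conditional form. Billing is the sole stated cost source, and it does not guarantee the quantity that the article itself defines. If the psychoeducation and CBT sessions are unbilled, the omission falls on STEP alone and moves both the ICER and the dominance rule in its favour.

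Under the assumptions above, the ICER would be too low by SGD 12,500 to 45,000 per QALY at a gain of 0.02, and by SGD 6,250 to 22,500 at 0.04. An error of that order is large enough to matter against the stated threshold. If the sessions are fully billed, there is no omission and one confirming sentence is enough. The point should be settled before the economic analysis, because the results are meant to support a cost-effective model of care.

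**What to change.** In Specific aims (outcomes under Aim 3) and in Data analysis (Aim 3), define STEP cost as billed care plus intervention delivery cost, where delivery cost is the number of sessions attended times a psychologist unit cost. Exclude costs incurred only for research, and exclude any session that already appears in the billing records, so that nothing is counted twice. Vary the unit cost in a sensitivity analysis. If the sessions turn out to be billed in full, say so; the added term is then zero.

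The cost is small. The completer definition in Data analysis depends on completed psychoeducation and on four of five CBT sessions, so attendance has to be recorded anyway, although the article describes no session log. One unit cost has to be obtained. Treatment, assessments and sample size do not change. The downside is that the ICER may come out less favourable to STEP.
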